### Procedure for unblinding if needed{17b}

The study is primarily an open-label trial with only outcome assessors being blinded so there is no need for an unblinding procedure.

## Data collection and management

### Plans for assessment and collection of outcomes {18a}

Data collection will be performed by one of the investigators of study who will be trained in how to do assessments. Subjects will be familiarized with the equipment and tests of study during screening. For all participants, data collection will be conducted at a certain time before noon, in face-to-face meetings at the motor control laboratory at the School of Rehabilitation of TUMS.

Participants will receive a SMS text or an email to remind their appointment the day before. Principal investigator of the study will supervise data collection to check the quality, completeness, plausibility, and possible errors of the collected data.

### Plans to promote participant retention and complete follow-up {18b}

The commuting expenses of the participants will be paid and flash memories will be provided to thank them.

### Data management {19}

At the beginning of the study, participants will be assigned a unique identification code and the data sent to the study assessor will only include the code without participant identification information. Subjective assessments and demographic information collected on paper forms will be entered into specific Excel files and a second study staff member will check the data entry process for accuracy. All paper-based data for the study including consent forms, identifiable information, and questionnaires will be kept separate from each other in a locked cabinet in the motor control laboratory at the School of Rehabilitation of TUMS. The electronic records of the study, i.e., raw data of EEG, Entropy, and the Excel files stored on a password-protected external hard drive and computer. Both paper and digital documents will only be accessible to the research team.

### Confidentiality {27}

To protect the privacy of all participants, they will be allocated an individual trial identification code, the research data will be stored on a password-protected external hard drive and computer and only members of the study team will access to the data.

### Plans for collection, laboratory evaluation, and storage of biological specimens for genetic or molecular analysis in this trial/future {33}

See above 26b- there will be no biological specimens stored in this research study.

## Statistical methods

### Statistical methods for primary and secondary outcomes {20a}

Data analysis will be performed using SPSS, version 22 (IBM, NY, USA). Baseline characteristics such as age, weight, height, BMI, years of computer use, and daily computer usage will be summarized with standard descriptive statistics. Depended variables will be described with means and standard deviations. The normality of distribution will be checked by Kolmogorov–Smirnov.

Multivariate ANOVA (MANOVA) will be used to compare the variables between correct and slump posture groups.

Statistical analysis of the outcomes of 3 conditions in the slump posture group will be conducted using repeated measures ANOVA and LSD (least significant difference) post hoc test. The significance level of tests will be considered at 0.05. Mean difference and standardized mean difference and their 95% confidence intervals (Cohen’s D) will be calculated as effect sizes.

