**Methods:**

The sample size for this study is set at 36 participants with slump posture and 36 participants with normal posture. In the first step, to find out the differences between normal and poor posture, they will be asked to perform the typewriting task for 60 min. During the first and last 3 min of typing, mental fatigue as the primary outcome using EEG signals and further measures including kinematic behavior of neck, visual analog fatigue scale, and musculoskeletal discomfort will be assessed. Post-experiment task performance will be calculated based on typing speed and typing errors. In the next step, to compare the effect of tDCS and stretching exercises on the outcome measures, the slump posture group will receive these interventions in two separate sessions before the typing task.

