### Objectives {7}

The main objective of this study is to compare the mental fatigue through EEG during a prolonged typing task (i.e., 60 min) between subjects with slump and normal postures and to determine whether using tDCS or stretching exercises in the slump posture group, can deal with mental fatigue and minimize the difference in terms of mental fatigue between slump and normal posture groups.

Secondary objectives of the study include the following:To compare the kinematic parameters (i.e., entropy of neck motion and cervical angle), task performance (i.e., typing speed and errors), musculoskeletal discomfort, and visual analog fatigue scale between subjects with slump and normal postures.To compare the kinematic parameters (i.e., entropy of neck motion and cervical angle), task performance (i.e., typing speed and errors), musculoskeletal discomfort, and visual analog fatigue scale between slump posture following performing stretching exercise and normal posture.To compare the kinematic parameters (i.e., entropy of neck motion and cervical angle), task performance (i.e., typing speed and errors), musculoskeletal discomfort, and visual analog fatigue scale between slump posture following tDCS and normal postureTo compare the kinematic parameters (i.e., entropy of neck motion and cervical angle), task performance (i.e., typing speed and errors), musculoskeletal discomfort, and visual analog fatigue scale between 3 conditions of stretching exercise, tDCS, and no intervention in slump posture group.

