#### Electroencephalography

The brain activities will be recorded using a 64-channel EEG system (EB Neuro, Italy) with a sampling rate of 1024 Hz and bandwidth of 0.2–70 Hz. The Ag/Ag Cl surface electrodes with a diameter of 8 mm and an impedance of less than 20 kHz, will be distributed throughout the whole head of the participants. The 21 electrodes, according to the international 10/20 system, will be placed in Fp1, Fpz, Fp2, F7, F3, Fz, F4, F8, T3, C3, Cz, C4, T4, T5, P3, Pz, P4, T6, O1, Oz, O2. A reference and ground electrode will be placed on the mastoid process and the wrist of the right hand respectively. To record vertical and horizontal eye movement, a pair of electrodes will be placed above and below the right eye and a pair of electrodes will be placed at the corner of each eye. Blinking and eye movement artifacts will be monitored with the electrooculogram and the O1 and O2 electrodes. The EEG will be recorded for 3 min under two conditions: while subjects will rest with their eyes open and while they will be typing, during the first and last 3 min of continuous typing. Thereafter, raw EEG data will be imported into LORETA version 2015–12-22 to extract the frequency domains (i.e., Fast Fourier transform, FFT) for delta, theta, alpha, beta, and gamma rhythms, by 1024 sampling frequency and two epochs (2048) for 21 electrodes. Then the relative power levels of each band will be calculated.

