## Discussion

To the best of our knowledge, this is the first study to investigate the impact of poor posture on mental fatigue.

Different techniques have been employed to measure mental fatigue. These methods are classified subjectively, behaviorally, and physiologically [43].

Subjectively, decreased energy [8], alertness [44], or motivation [45] with an increase in feelings of tiredness [8] are the characters of mental fatigue. In this method, standard questionnaires such as F-VAS have been used [43]. Behaviorally, performance deterioration including decreased in accuracy and slower responses, occurs following mental fatigue [9, 10, 46]. Effects of mental fatigue on performance have been studied since the beginning of the nineteenth century; Different theories about cognitive mechanisms have been proposed in this issue. According to these studies, people begin to experience mentally tired and their performance deteriorates when the costs of doing a task overtake the benefits of finishing that task [13]. Performance can be measured in different ways; For employees who are prone to mental fatigue, computer typing provides information about the level of mental fatigue without interfering with regular work activities [13, 47]. Physiologically, mental fatigue is detected by tracking alternations in the neural activity of the cortex [9, 48–50]. EEG spectral band change has been considered a reliable biomarker to detect mental fatigue. Increased slow-band EEG activity (i.e., 4–13 Hz), is associated with decreased mental activity [7].

Recent studies have revealed that mental fatigue has a negative effect on neuromuscular function including strength, muscle activity, and joint steadiness [51]. According to Marcora et al. (2009), during the condition of mental fatigue, people experience greater discomfort, decreased muscle endurance, and a higher perception of effort [46]. These changes in neuromuscular function may lead to loading of the musculoskeletal system and changes in kinematic parameters.

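### The protocol fixes neither a primary EEG variable nor the MANOVA's dependent variables; the full EEG set cannot be fitted jointly at N = 72, and splitting it by band or electrode gives several unadjusted primary tests

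*Protocol article*

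**What the plan says.** The abstract's Methods paragraph gives "mental fatigue as the primary outcome using EEG signals". Objectives {7} states "The main objective of this study is to compare the mental fatigue through EEG during a prolonged typing task" between the slump and normal posture groups.

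The only operational definition is in the Electroencephalography part of Outcomes {12}. Spectra are extracted "for delta, theta, alpha, beta, and gamma rhythms", "by 1024 sampling frequency and two epochs (2048) for 21 electrodes", and "Then the relative power levels of each band will be calculated". The denominator of relative power and the band limits are not given. Trial design {8} places all outcome measurements at T1 and T2, the opening and closing three minutes of typing. An eyes-open resting EEG is also recorded.

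For Part 1, Statistical methods {20a} says "Multivariate ANOVA (MANOVA) will be used to compare the variables between correct and slump posture groups". It sets the significance level at 0.05, does not list the variables and states no adjustment for multiple tests. Sample size {14} calculates 50 participants for Part 1 (one-tailed alpha 0.05, power 0.90) and raises the total to 72, 36 per group.

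The one pointer to a band of interest is background in the Discussion: "Increased slow-band EEG activity (i.e., 4–13 Hz), is associated with decreased mental activity".

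**The concern.** The primary outcome is a construct measured by a large grid of band-by-electrode values, and the method attached to it is a multivariate test of unlisted variables. A two-group MANOVA needs an invertible within-group error matrix, which is impossible when the dependent variables outnumber the error degrees of freedom. If the grid is too large for one model, someone must reduce or split it, and the protocol does not say how. The choice of bands, sites and time contrast could then be made with the data in hand, across several tests each run at 0.05. A claim on the main objective could rest on whichever band or site happened to reach significance.

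**Working it through.** **Inputs.** Bands: 5; electrodes: 21 (Electroencephalography). Typing time points: 2 (Trial design {8}). Participants: 72, or 50 before the dropout allowance (Sample size {14}). Test level: 0.05 (Statistical methods {20a}).

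**The plan's own figure.** The 50 cannot be reproduced, because no effect size, standard deviation or outcome variable is given. Solving backwards for a two-sample t test with 25 per group and 90% power gives a standardised difference of 0.84 one-sided or 0.94 two-sided. For a MANOVA global test at N = 50, the multivariate (Mahalanobis) distance needed for 90% power depends on the number of variables: 0.94 for one, 1.17 for four, 1.85 for 21. So the meaning of the 50 depends on a variable set that is not stated.

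**Size of the full set.** 5 × 21 = 105 variables per time point; with T1 and T2, 2 × 105 = 210. Dropping one band at each electrode leaves 4 × 21 = 84.

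**Can it be fitted jointly?** With two groups, the rank of the error matrix is at most the smaller of the number of variables and N − 2.
- N = 72: 70 error df, against 105 or 84 variables. Singular.
- N = 60: 58 error df. Singular.
- N = 50: 48 error df. Singular.

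Simulated relative powers gave the same ranks: 70 for both the 105- and the 84-variable set at N = 72, and 58 and 48 at the smaller sizes. This result does not depend on how relative power is normalised.

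**What can be fitted?**
- One MANOVA per band: 21 variables, rank 21, within 70 df. Five tests.
- One MANOVA per electrode on four bands: 21 tests.
- One MANOVA on four bands averaged over electrodes: rank 4. One test per time point, but the protocol does not state this averaging.

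**Error rate of the splits.** If the k tests are independent, the familywise error is 1 − 0.95^k.
- k = 5: 1 − 0.95^5 = 0.226.
- k = 21: 1 − 0.95^21 = 0.659.
- T1 and T2 tested separately: k = 10 gives 0.401 and k = 42 gives 0.884.

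EEG variables are correlated, so the true rates are lower than these. Correlation does not bring them under control.

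**Sum-to-one redundancy (assumption).** If the denominator is the sum of the five bands, the five values at an electrode sum to 1. A MANOVA using all five then has an error matrix of rank 4 and is singular. If the denominator is total power over the recorded range and the bands do not cover that range exactly, this need not occur.

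**The case against.** The strongest reply is that the protocol never says all 105 values enter one model. It speaks only of unlisted variables, and sensible smaller models exist. This stands. A reader might infer that the main objective has no computable test, or that the plan amounts to 105 or more unadjusted univariate tests, with 105 × 0.05 = 5.25 false positives expected under a global null. The documents support neither reading: the first is true only of the joint model, and the second is a worst case that the protocol does not state. Nor can the sum-to-one singularity be taken as fact, since the denominator is not given.

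Second, Trial design {8} calls Part 1 exploratory, which would soften the need for strict error control. That carries some weight. However, Objectives {7} makes the same comparison the main objective, and Sample size {14} powers it at 0.90 with alpha 0.05. The abstract's Discussion expects the findings to provide evidence of an adverse effect of poor posture on mental state. These are confirmatory uses.

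Third, electrode grouping, the list of dependent variables and multiplicity handling often sit in a statistical analysis plan, which is not shown here. Their absence alone would not be a finding. The point is that the article does commit to a primary outcome and to a method, and the two do not fit together as written. Averaging over electrodes would give a single test at each time point, but it is a choice still to be made, and a significant result would not show which band differs.

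**Conclusion.** The concern holds in this form: the primary EEG variable, its time contrast and the MANOVA's dependent variables are not fixed, and the stated method does not fit the outcome as defined. The joint model is ruled out by counting alone (105 or 84 variables against 70 error df at full enrolment, 48 at the 50 calculated as needed). Splitting by band or by electrode leaves 5 or 21 primary tests at an unadjusted 0.05, with familywise error of about 0.23 or 0.66. Those two rates assume independence and are upper guides. The further singularity within an electrode holds only if relative power is taken over the sum of the five bands. Because this affects what Objectives {7} calls the main objective, it should be settled before the EEG data are compared between groups.

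**What to change.** - **Primary variable.** Pre-specify one EEG variable and one contrast. An example that follows the Discussion's own rationale is 4–13 Hz relative power, with its denominator stated, averaged over a fixed electrode set. Compare the change from T1 to T2 between the posture groups, once, at 0.05.
- **Other EEG results.** Report the remaining bands and sites as secondary, with Holm or false-discovery-rate control.
- **MANOVA.** If it is kept, limit it to a small fixed set of region-averaged bands with one band omitted, and list its dependent variables.
- **Sample size.** State whether the calculation in Sample size {14} refers to this variable. If it does not, give the effect size and the precision that the planned number provides for it.
- **Status of Part 1.** Reconcile the exploratory label in Trial design {8} with the main objective in Objectives {7}.

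**Cost.** No new recordings are needed, since T1 and T2 EEG at all 21 electrodes is already planned. The work is a dated change of wording and a check of the sample size against the named variable. The downside is that single-electrode findings lose confirmatory status.

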### Interim analyses {21b}

There will be no stopping guidelines and interim analyses, as this is a low-risk study with no anticipated problems for participants.

### Methods for additional analyses (e.g., subgroup analyses) {20b}

There will be no additional analyses for the present study.

### Methods in analysis to handle protocol non-adherence and any statistical methods to handle missing data {20c}

Outcome data obtained from protocol non-adherence will not be considered in the study. We will make all efforts to avoid missing data and conduct analysis on complete cases; however, if missing data is more than expected (more than 5%), an intention-to-treat analysis will be performed.

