### Criteria for discontinuing or modifying allocated interventions {11b}

If subjects report seven or higher level of itching, tingling, and heat based on 10-point Likert scale, tDCS will be stopped.

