### Sample size {14}

Based on pilot data of 12 subjects (i.e., 6 cases for slump posture and 6 cases for normal posture), the sample size was calculated using G*Power 3.1.9.4 (Düsseldorf, Germany) software. Sample size estimation was conducted according to one-tailed testing with an alpha set at 0.05 and the desired power of 0.90. For the first part of the study, a sample size of 50 participants distributed in two groups was estimated. For the second part, we calculated that 30 subjects with slump posture, are needed.

To consider a potential 20% drop-out rate, the sample size is 72 participants (36 in each group).

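### The rule for the analysis population changes with the amount of missing data, contradicts itself on non-adherence, and its 5% trigger sits badly with the 20% drop-out margin

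*Protocol article*

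**What the plan says.** Section {20c} of the Protocol article sets the population in two sentences.

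- **Non-adherence:** "Outcome data obtained from protocol non-adherence will not be considered in the study". No condition is attached and non-adherence is not defined.
- **Default:** the investigators will "conduct analysis on complete cases".
- **Switch:** "if missing data is more than expected (more than 5%), an intention-to-treat analysis will be performed". The section does not say whether the 5% counts participants, sessions or values, or how missing values are treated after the switch.

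Three other sections bear on this.

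- **Sample size {14}:** "For the second part, we calculated that 30 subjects with slump posture, are needed", and then "To consider a potential 20% drop-out rate, the sample size is 72 participants (36 in each group".
- **Statistical methods {20a}:** the analysis of the three slump conditions "will be conducted using repeated measures ANOVA and LSD (least significant difference) post hoc test".
- **Discontinuation {11b}:** "If subjects report seven or higher level of itching, tingling, and heat based on 10-point Likert scale, tDCS will be stopped".

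No other section of the article fixes an analysis population, and {20b} plans no additional analyses.

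**The concern.** This is a stated rule, not a detail left to a later analysis plan, and it has three faults.

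1. The choice between two populations is made after the extent of missing data is known. With the unit of the 5% undefined, there is room to argue afterwards about which side of the line the trial fell.
2. The rule contradicts itself. Intention-to-treat keeps participants as randomised whatever their adherence, whereas the first sentence removes non-adherent data in every case.
3. The fallback names whom to analyse but not what to do about missing sessions. With the stated ANOVA it may bring back the complete-case analysis it was meant to replace.

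The second part of the study is its only randomised comparison. Exclusions made there after randomisation decide to whom the result applies. The objectives also compare slump participants after each intervention with normal-posture participants, who attend only once. A filter that requires all three sessions therefore acts on one side of that comparison only.

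**Working it through.** **Inputs.** From {14}: 30 slump participants needed, 36 planned per group, 72 in total, 20% drop-out margin. From {6b}: three sessions per slump participant, so 36 × 3 = 108 sessions. From {20c}: trigger at more than 5% missing.

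**Reproducing the planned size.** 30 × (1 + 0.20) = 36, which matches the plan. (30 / (1 − 0.20) = 37.5 would round up to 38.) At 20% loss, 36 × 0.80 = 28.8 complete slump participants remain, just under the 30 required.

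**Where the trigger falls.** 5% of 36 is 1.8, so 2 participants (5.6%) cross it and 1 (2.8%) does not. 5% of 72 is 3.6, so 4 cross it. 5% of 108 sessions is 5.4, so 6 cross it. Counted in slump participants, one person can decide which population is analysed.

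**Chance of crossing it, counting participants.** With X binomial(36, 0.20):

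P(X ≥ 2) = 1 − 0.8^36 − 36 × 0.2 × 0.8^35 = 1 − 0.0003 − 0.0029 = 0.997.

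For all 72, P(X ≥ 4) = 0.9999. The 20% is a margin and actual loss may be lower, so the range matters:

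| Assumed loss of participants | 2 or more of 36 | 4 or more of 72 |
|---|---|---|
| 2% | 0.16 | 0.06 |
| 5% | 0.54 | 0.49 |
| 10% | 0.89 | 0.94 |
| 20% | 0.997 | 0.9999 |

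**Chance of crossing it, counting sessions.** Assume sessions are lost independently, and that 20% of participants miss at least one. Then the loss per session is q = 1 − 0.8^(1/3) = 0.0717. With X binomial(108, 0.0717), P(X ≥ 6) = 0.79.

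**Valid sessions discarded by complete-case ANOVA at 20% loss.** Here 36 × 0.20 = 7.2 participants are incomplete, and every session they did attend is dropped.

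- All withdraw before session 1: 7.2 × 0 = 0.
- All withdraw after session 1: 7.2 × 1 = 7.2.
- All withdraw after session 2: 7.2 × 2 = 14.4.
- Independent loss per session: 108 × (1 − 0.0717) = 100.3 observed, 36 × 0.8 × 3 = 86.4 used, 13.9 discarded.

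The range is therefore 0 to about 14.

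**Small losses build up over three sessions.** Independent loss of 2% per session makes 1 − 0.98³ = 5.9% of participants incomplete; 5% per session makes 1 − 0.95³ = 14.3% incomplete.

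**The case against.** The case on the other side has several strands.

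- **The 20% is a recruitment margin for a potential loss, not a forecast.** Drop-out of people and percentage of missing data are also different quantities. {10} lists people unwilling to continue among its exclusions, so the 5% might refer to gaps among those retained. This stands. The two figures sit badly together but are not a strict contradiction, and the 0.997 holds only if the 5% counts participants and 20% are lost.
- **If the switch is almost certain, the population hardly depends on the data.** That is fair at 20% loss. At losses of 2% to 10% the outcome is open, and one participant can decide it.
- **The threshold is set in advance and the analyst is blind to groups and conditions.** This stands too: the switch follows the amount missing, not the results. It does not remove the conflict between the two sentences.
- **Handling of missing values under intention-to-treat may be left to a fuller document.** That is so, and the article does not say that the fallback is complete-case. But the removal sentence and the switch are explicit, so a later plan would have to overturn them, not merely add detail.

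A reader might also infer that the tDCS effect will be estimated only in people who tolerate it, to its advantage. The document does not support that. It never says that a session stopped under {11b} counts as non-adherence, and stopping under a protocol rule could equally be called adherence. No stopping rule is given for stretching. In a within-person crossover, complete-case analysis compares the same people under all conditions. Its main effect is on who is represented, and the tDCS-versus-stretching contrast need not lean towards either.

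**Conclusion.** The concern holds. The population depends on the observed amount of missing data, and unconditional removal of non-adherent data contradicts the intention-to-treat fallback. Both follow from {20c} alone, with no numerical assumption.

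The mismatch with the sample size is real but conditional. If 20% were lost, the switch would occur with probability about 0.997 counting slump participants, or about 0.79 counting sessions with independent loss. Between 0 and about 14 valid sessions would be discarded if ANOVA in its standard form is used. That is a loss of efficiency, not a measure of bias.

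If stopped tDCS sessions are treated as non-adherence, people who tolerate tDCS poorly would leave the randomised comparison. The document leaves this open, and neither the size nor the direction of any resulting bias can be computed from it.

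**What to change.** Delete the 5% switch and the sentence that removes non-adherent data. Name one primary set before any data are seen: all randomised slump participants, by assigned sequence, with every available session whatever the adherence, plus all enrolled normal-posture participants with outcome data. Analyse the three slump conditions with a likelihood-based linear mixed model, which keeps participants with one or two sessions and runs in the SPSS package already named in {20a}. Define non-adherence, including whether a session stopped under {11b} counts, and report the adherent complete-case analysis as a sensitivity analysis only.

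The change needs no extra data and no change to the sample size. It costs slightly more analysis work, and the estimated effect will include non-adherent sessions, which the report should say.
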